#### **6.2.2 Exclusion Criteria**

- Planned two-stage esophageal reconstruction or planned total laryngectomy
- Meets contraindications for EX-1 Medic® EMT device, including: frequent asthma exacerbations; tympanic membrane perforation or similar injury; markedly elevated LV end-diastolic volume/pressure; worsening (or high likelihood) of heart failure signs/symptoms after respiratory muscle training per physician judgment; history or suspected costochondritis
- Active infection or other serious comorbidity such that EMT may increase dyspnea due to respiratory muscle fatigue, reduce consciousness due to hyperventilation, or cause syncope due to rapid hemodynamic changes associated with intrathoracic pressure shifts, as judged by the attending physician
- Difficulty enrolling due to disorientation or psychiatric illness
- High risk of pneumothorax or high physical burden from EMT due to severe emphysematous lesions or giant bullae, judged by investigators prior to surgery
- Serious conditions such as severe pneumonia, heart disease, severe liver disease, severe kidney disease; history of cardiac complications within 1 month (unstable angina, myocardial infarction, percutaneous coronary intervention, coronary artery bypass grafting) or cerebrovascular disease within 6 months; or severe emphysema/giant bullae

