###### **Intervention group (EMT):**

- Device instruction and load adjustment during the neoadjuvant therapy period
- Load starts at 50% of maximal expiratory pressure and is progressively increased up to 75%
- 30 breaths per set; 2–3 sets/day; completion criterion: ≥5 days/week

Both groups will use a training log to record daily sessions and repetitions.

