#### 8.3.2 Adverse Events

Definitions:

Serious: falls/fractures, cardiopulmonary arrest, death.

Non-serious: hypotension, unsteadiness, dizziness, malaise.

Known: dyspnea, anxiety, palpitations, lower-limb fatigue.

Causality: Adverse events occurring during study procedures (assessment/measurement) are considered related.

Follow-up items when an adverse event occurs: symptoms/findings, onset date, outcome (A=recovered; B=improved; C=unchanged; D=recovered with sequelae; E=death), and outcome date.

Reporting: In the event of a serious or unexpected adverse event, the Principal Investigator will report to the Dean in accordance with institutional regulations. If an adverse event meets criteria for urgent reporting, sub-investigators will immediately notify the Principal Investigator.

Depending on frequency and severity, enrollment may be suspended or the trial interrupted/terminated at the discretion of the study leadership.

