### **10.4 Participant Burden, Risks, and Benefits**

The only assessment performed solely for this study is ultrasound measurement of laryngeal elevation distance and suprahyoid muscle cross-sectional area. Other interventions, examinations, and assessments performed during hospitalization (pre/postoperative) are within routine insured medical care and do not incur costs beyond usual patient co-payments. Ultrasound assessments will be conducted with the hospital director's approval for use of hospital-managed equipment, and no costs will be charged to participants.

The EMT device (EX-1 Medic®) will be purchased using research funds of [name] and provided to participants. Consumable and equipment-related costs for assessments (see the separate cost calculation document) will be covered by allocated research funds of [name]. Potential risks include adverse events during assessments; because assessments are conducted during routine clinical hours, physician support from the Department of Rehabilitation Medicine will be available if needed.

Participants will receive the EMT device as a gift; otherwise, there are no direct individual

benefits. However, study findings may contribute to future improvements in care for patients with esophageal cancer.

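### The only causality rule for adverse events names assessments and measurements but omits the EMT and sham sessions, so an event arising in training has no related class

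*Protocol*

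**What the plan says.** Section 8.3.2 states: "Causality: Adverse events occurring during study procedures (assessment/measurement) are considered related". No other part of the protocol gives a causality rule or provides for case-by-case judgement of causality. Section 10.4 has the same focus: "Potential risks include adverse events during assessments". It does not mention training as a source of risk.

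Training is described in section 6.2.5. Both arms have the same frequency ("30 breaths per set; 2–3 sets/day; completion criterion: ≥5 days/week") and differ in expiratory load. On record-keeping the section says: "Both groups will use a training log to record daily sessions and repetitions".

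Section 6.2.2 recognises hazards of training. It excludes patients whose infection or comorbidity means that "EMT may increase dyspnea due to respiratory muscle fatigue, reduce consciousness due to hyperventilation, or cause syncope due to rapid hemodynamic changes", and those with "High risk of pneumothorax or high physical burden from EMT due to severe emphysematous lesions or giant bullae". It also lists likely worsening of heart failure after respiratory muscle training among the device contraindications.

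On escalation, section 8.3.2 says: "In the event of a serious or unexpected adverse event, the Principal Investigator will report to the Dean in accordance with institutional regulations".

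**The concern.** A causality rule should reach the exposure under test. Here the exposure is weeks of loaded expiratory training against sham, and the rule is written around the measurements, which both arms undergo alike. If investigators apply the bracket literally, a fainting episode during an EMT set has no route to being called related, while the same episode during an exercise test is related automatically.

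At stake is the safety information this phase II trial passes on. Section 5.0 says its effect estimate will be used to design a multicentre study. If events in training are left unclassified, the account of related harms handed to that study could omit those of the intervention. Section 11.4 provides for no monitoring or audit that might catch this.

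**Working it through.** No arithmetic applies: the protocol gives no adverse-event rate and no figure that depends on this rule. The check sets the relevant sections side by side.

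1. **What the rule covers.** Section 8.3.2 ties relatedness to study procedures and explains that term as assessment or measurement. Training is neither. The bracket therefore leaves it out, although the word *only* does not appear.

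2. **Whether another rule fills the gap.** The sections on interventions (6.2.5), assessments (6.5.3), schedule (6.6), risks (10.4), reporting (10.5) and monitoring (11.4) contain no causality rule. Section 10.4 repeats the focus on assessments.

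3. **Whether training is background care.** The sections disagree. Section 6.2.4 places the study within routine insured preoperative rehabilitation, and section 10.4 describes interventions during hospitalisation as routine insured care. Section 6.6 separates the two phases: postoperative rehabilitation is usual practice, and preoperative rehabilitation is done for the trial. Randomising the training load also makes it a study intervention. The routine-care wording therefore does not justify leaving it out of the rule.

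4. **Whether the protocol expects training to be able to cause harm.** Section 6.2.2 names dyspnoea, reduced consciousness, syncope, pneumothorax and worsening heart failure in connection with EMT or respiratory muscle training, in each case for susceptible patients.

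5. **Whether those hazards are in the event definitions.** Section 8.3.2 reads "Known: dyspnea, anxiety, palpitations, lower-limb fatigue", so dyspnoea is listed. Dizziness, low blood pressure and falls appear in its other lists. Syncope, reduced consciousness, pneumothorax and heart failure appear in none.

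6. **Whether symptoms in training would be recorded.** The log is described as holding sessions and repetitions. No symptom entry is mentioned.

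7. **What does not depend on the rule.** The follow-up items apply whenever an adverse event occurs. Reporting to the Dean is triggered by a serious or unexpected event. Suspension depends on how often and how severely events occur. None of the three is filtered by relatedness.

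Steps 1 to 4 establish the gap. Steps 5 and 6 show that the event lists and the log do not make up for it. Step 7 limits its reach.

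**The case against.** The strongest reply is that the sentence gives a sufficient condition. Events during assessments are related; nothing says that other events are unrelated. That is correct. Training events are left without a class, not declared unrelated. But a rule that is silent on the randomised exposure, with no provision for judgement elsewhere, still leaves investigators nothing to apply.

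A second reply is that section 6.2.2 describes patients who are kept out of the trial, so its hazards are not a harm profile for those enrolled. This also stands. The section shows that the protocol regards EMT as capable of causing these events, not that they are expected in participants.

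Several stronger readings are tempting and are not supported:

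- *Suspension decisions would rest on the wrong events.* Section 8.3.2 bases suspension on frequency and severity, not relatedness.
- *Serious harms of training would go unreported.* Serious or unexpected events are reported whatever their cause.
- *A planned comparison of related events between arms would be biased.* The protocol plans no such comparison, and the tabulation of adverse events may properly be left to an analysis plan.
- *The weekly number of training breaths measures the defect.* It measures training volume, not misclassified events, and the frequency in section 6.2.5 is a completion criterion, not a guaranteed minimum.
- *The uncovered events happen at home.* The protocol does not say where training takes place.

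**Conclusion.** The point holds as a defect in a rule that the protocol itself fixes. The causality definition omits the intervention being tested and conflicts with sections 6.2.2 and 6.6. A harm of EMT could therefore go unattributed, and a non-serious one might not be recorded if symptoms have no place in the log.

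Its extent is the training of all 40 planned participants, 20 per arm. Its size in events cannot be stated, because the protocol gives no rate.

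The conclusion rests on two assumptions: that investigators would read the bracket as defining study procedures and not merely as an example, and that no separate safety manual supplies a broader rule. The consequence is confined to attribution and possibly detection. The protocol should be amended, but its handling of serious or unexpected events does not fail.

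**What to change.** Reconcile sections 8.3.2 and 10.4 with sections 6.2.2, 6.2.4 and 6.6:

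- **Causality rule (8.3.2).** Treat adverse events with onset during an EMT or sham session on the same footing as those during an assessment. Have later events in the training period assessed case by case for relationship to training, by someone blind to arm where possible. Do not class every event after a session as related: with no time limit, that would take in later neoadjuvant toxicity and surgical complications.
- **Risk statement (10.4).** Name training sessions as well as assessments as a source of risk, and state consistently whether preoperative training is routine care or a study intervention.
- **Training log (6.2.5).** Add an entry for symptoms or adverse events.
- **Event definitions (8.3.2).** If the hazards in section 6.2.2 are added, keep them off the list of known events, or state that they remain reportable. The protocol does not define *unexpected*; if it means not listed as known, listing syncope or pneumothorax there could remove their reporting trigger.

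The cost is a protocol amendment with ethics review, one extra line in a log already in use, and slightly more event review. No training load, schedule or stopping rule changes.

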## **9.0 Scientific Rationale and Study Limitations**

### **9.1 Scientific Rationale**

If preoperative EMT is shown to attenuate postoperative decline in swallowing function in patients with esophageal cancer, it will provide evidence supporting swallowing-focused interventions as part of preoperative rehabilitation.

### **9.2 Limitations**

- Not double-blinded.
- Short postoperative follow-up period.
- At the time of allocation, the degree of surgical invasiveness for individual patients may not be fully known.

## **10.0 Ethical Considerations**

### **10.1 Ethical Principles and Guidelines**

All investigators will conduct the study in accordance with the Declaration of Helsinki and the Ethical Guidelines for Life Science and Medical Research Involving Human Subjects.

### **10.2 Informed Consent**

Written informed consent will be obtained. Investigators will provide the participant information sheet and consent form, ensuring understandable language, and explain the study both in writing and verbally. After confirming participant understanding, written consent will be obtained via signature. Participants may withdraw consent at any time, and withdrawal requests will be honored.

### **10.3 Protection of Personal Information**

Personal information handling will comply with the Ethical Guidelines, the Act on the Protection of Personal Information, and applicable laws/regulations. Data will be processed so that individuals cannot be identified, and a correspondence table (linkage key) will be created and retained within the university until the end of the retention period. Data will be stored on a computer not connected to the network and recorded to external storage (e.g., USB) kept in a locked cabinet. Study results will be published without identifiable information, and data will not be used for purposes other than this study. Direct identifiers (name, date of birth, etc.) will be removed to prevent re-identification.

The custodian of the correspondence table at Kindai University Hospital will be: [name], Department of Rehabilitation, Kindai University Hospital.

### **10.4 Participant Burden, Risks, and Benefits**

The only assessment performed solely for this study is ultrasound measurement of laryngeal elevation distance and suprahyoid muscle cross-sectional area. Other interventions, examinations, and assessments performed during hospitalization (pre/postoperative) are within routine insured medical care and do not incur costs beyond usual patient co-payments. Ultrasound assessments will be conducted with the hospital director's approval for use of hospital-managed equipment, and no costs will be charged to participants.

The EMT device (EX-1 Medic®) will be purchased using research funds of [name] and provided to participants. Consumable and equipment-related costs for assessments (see the separate cost calculation document) will be covered by allocated research funds of [name]. Potential risks include adverse events during assessments; because assessments are conducted during routine clinical hours, physician support from the Department of Rehabilitation Medicine will be available if needed.

Participants will receive the EMT device as a gift; otherwise, there are no direct individual

benefits. However, study findings may contribute to future improvements in care for patients with esophageal cancer.

### **10.5 Reporting Requirements**

The Principal Investigator will report to the Dean using designated forms in the following situations:

- (1) Annual progress report on study implementation.
- (2) Study completion (or discontinuation/suspension) report.
- (3) Deviation report when learning of information/facts that compromise ethical validity or scientific rationale, or could affect study continuation.

## **11.0 Administrative Considerations**

### **11.1 Data Handling**

#### **11.1.1 Data Storage and Disposal**

Data will be stored until the later of (a) at least 5 years after study discontinuation/completion, or (b) 3 years after publication of study results.

#### **11.1.2 Secondary Use of Data**

This study may involve secondary use of participant data obtained for research purposes. If secondary use is planned, a new research plan will be developed and must be reviewed and approved by the Ethics Committee and authorized by the Dean prior to use.

### **11.2 Funding and Conflicts of Interest**

#### **11.2.1 Funding**

Study funding sources: allocated research funds of [name] (Department of Rehabilitation Medicine, Faculty of Medicine, Kindai University) and research funds of [name].

#### **11.2.2 Conflict of Interest Management**

All investigators will disclose conflicts of interest in accordance with institutional policies. The study can be conducted only after review and approval by the COI Committee. Any changes will be reported promptly via an amendment application.

### **11.3 Public Disclosure**

#### **11.3.1 Dissemination of Study Information**

After study completion, results will be published in scientific journals and/or presented at academic conferences with appropriate protections for participant privacy. The study will be registered in the UMIN-CRT system and assigned an ID.

#### **11.3.2 Intellectual Property**

If economic benefits such as patent rights arise from this study, the rights belong to Kindai University and not to study participants.

#### **11.3.3 Handling of Incidental Findings**

Incidental findings that are clinically relevant may be discovered through study assessments. In such cases, the participant will be informed and, if necessary, referred to an appropriate specialist for consultation.

### **11.4 Monitoring and Audit**

This study is considered non-invasive and will not conduct monitoring or audits.

